**2. INTRODUCTION**

**2.1 STUDY RATIONALE**

Inflammasomes are large multimeric protein complexes that actively regulate immunity and homeostasis through sensing and responding to microbial or other danger signals. The nucleotide-binding oligomerization domain-like receptor family pyrin 3 (NLRP3) inflammasome is expressed in immune cells of the gut and promotes inflammation through caspase-1-dependent cleavage and activation of immature pro-inflammatory cytokines interleukin (IL)-1β and IL-18 as well as by induction of pyroptotic cell death (de Zoete et al. 2014). Locally, IL-1β can induce cytokine production, enhance T-cell

activation and antigen recognition, and direct neutrophils to the site of injury. NLRP3 and IL-1β are both upregulated in active ulcerative colitis (UC; Tourkochristou et al. 2019). Several animal colitis model studies reported that inhibition of IL-1β function by methods that operate downstream of the NLRP3 inflammasome, resulting in reduced gut inflammation (Perera et al. 2018; Neudecker et al. 2017).

RO7486967 is a selective and reversible small molecule NLRP3 inflammasome inhibitor that has been shown to inhibit IL-1β release and cell death in vitro (see the RO7486967

Investigator Brochure [IB]).

This study will assess the safety, tolerability, and pharmacokinetics (PK) of RO7486967 and pharmacodynamic (PD) markers of inflammation in patients with moderate to severe active UC. The rationale for the study design is provided in Section 4.2.

**2.2 BACKGROUND**

**2.2.1 Ulcerative Colitis**

Ulcerative colitis is a chronic, relapsing disease characterized by diffuse mucosal inflammation of the colon. Moderate to severe UC is a debilitating disease that can result in hospitalization for disease flares, potential bowel perforation or hemorrhage, and increased risk of colorectal cancer. Current treatment goals include induction and maintenance of remission, improved quality of life, reduction in the need for long-term corticosteroids, and minimization of cancer risk. Management of UC includes initial use

of aminosalicylates (e.g., sulfasalazine or mesalamine) and/or corticosteroids to induce remission, or the use of biologic agents (e.g., tumor necrosis factor [TNF] inhibitors or integrin inhibitors) in patients with severe disease or in whom induction cannot be achieved with steroids. Once induction of remission has been achieved, maintenance therapy such as aminosalicylates, thiopurines (e.g., azathioprine or 6-mercaptopurine), or biologics (e.g., anti-TNF or anti-integrins monoclonal antibodies) are given with the aim of maintaining disease control and avoiding long-term steroid use. Patients with severe acute disease or severe refractory disease may be considered for surgery (e.g., colectomy).

Among multiple new molecular entities tested in patients with UC over the past two

anti-IL-12p40 (ustekinumab), and a pan-Jak inhibitor (tofacitinib) have demonstrated efficacy in patients with moderate to severe UC (Chang and Hudesman 2020).

Despite these recent additions to the treatment arsenal, over 70% of patients with moderate to severe UC still lack an effective, long-term therapy (Neurath 2017). Therefore, there is an urgent need for new treatments for UC in patients who do not respond to current treatment options.

**2.2.2 RO7486967**

The results of the entry-into-human (EIH) Phase 1 study IZD334-001 showed that RO7486967 appeared to be safe and well tolerated when administered to healthy male and female adult volunteers at single-ascending doses of 20 mg, 60 mg (fasted and fed),

180 mg, 450 mg, and 600 mg; and multiple-ascending doses (MAD) of 180 mg once daily (QD), 180 mg twice daily, and 450 mg QD for 7 days. The PK results showed rapid absorption of RO7486967, a half-life of approximately 7 hours, and no indication of a change in the exposure on repeat dosing for 7 days. The PD results showed that RO7486967 achieved the desired inhibition of IL-1β ex vivo whole blood lipopolysaccharide (LPS) and nigericin-induced IL-1β release assay.

A detailed description of the chemistry, pharmacology, and safety of RO7486967 is provided in the IB.

**2.3 BENEFIT/RISK ASSESSMENT**

Study BP43099 is the first study involving dosing of RO7486967 in participants with active UC to assess safety, the PK and PD effects at both the blood and gut tissue levels. A potential therapeutic effect on active UC will be limited as there is only 1 week of treatment duration. Safety data in healthy volunteers (HVs) from the EIH Study IZD334-001 are available and are summarized in the IB. Potential risks that had been identified based on clinical experience in HVs and non-clinical pharmacology and toxicology data in the relevant animal species will be closely monitored in this study.

The eligibility criteria, design and procedures adopted are considered to be appropriate for the safe conduct of the planned study. Participants will be closely monitored for safety (consistent with standard practices) and under close medical observation during the study.

The dose tested (i.e., 450 mg QD for 7 days) was the highest dose assessed in

Study IZD334-001 and was well tolerated.

Potential risks and plans for mitigation are detailed below.

• Hepatotoxicity: A battery of in vitro tests was conducted to assess the hepatotoxicity potential of RO7486967 and did not show mitochondrial toxicity,

on these in vitro assessments, the potential of RO7486967 to cause direct hepatotoxicity is considered low at therapeutically relevant concentrations. Consistently, no signs of hepatotoxicity were observed in the 26-week GLP study in the rat and 39-week GLP study in the monkey. During the MAD part of Study IZD334-001, 4 out of 18 healthy volunteers who received RO7486967 experienced a mild transaminase increase however there was no clear dose dependency and these abnormalities deemed not clinically significant by the Investigator. As a precautionary measure participants with impaired liver function will be excluded from enrollment, index of liver or biliary injury will be closely monitored during study. The management rules for abnormalities in liver function tests are detailed in the protocol (see Section 8.2.8).

• Infection: The NLRP3 inflammasome is a key component of the innate immune system that induces IL-1β production and cell death. NLRP3 is activated by a wide variety of signals (Coll et al. 2016). Blocking NLRP3 by RO7486967 will inhibit a single pathway among the several IL-1β production regulating mechanisms. Therefore, IL-1β production could still occur during infection when NLRP3 is inhibited. Consequently, blocking NLRP3 is expected to have a minimal immunomodulatory effect during infections. No evidence of bacterial, viral, fungal, and other opportunistic infections was found in rats and monkeys included in the nonclinical toxicology studies and in HVs in the Phase I clinical

study with RO7486967. As precautionary measures**,** patients with a known active

infection will be excluded from the study, and new/emerging infections will be closely monitored (see Section 8.2.8).

• Impaired immunization to vaccinations: many synthetic adjuvants activate NLRP3 in myeloid cells of the innate immune system, which promotes robust Th1 and

B-cell responses to vaccine antigens. Therefore, the inhibition of NLRP3 may affect the adaptive immune response produced by defined combination vaccine adjuvants (Seydoux et al. 2018). Therefore, patients who require vaccinations should complete any immunizations at least 4 weeks before first dose.

• The risks due to blood collection and rectal biopsy are regarded as minimal.

Participants might experience minor discomfort during the rectoscopy. Very rarely, rectal bleeding, pain, or infection after rectoscopy might occur.

An assessment was conducted to determine whether there is any impact of the

COVID-19 pandemic on the benefit/risk assessment of this study protocol, including (but not limited to) the patient population under study and study treatment being evaluated. On the basis of literature data (Shah A. 2020), SARS-CoV-2 viroporin protein 3a activates the NLRP3 inflammasome leading to the production of inflammatory cytokines resulting in tissue inflammation during respiratory illness caused by SARS-CoV-2 infection. NLRP3 inhibition may be beneficial during SARS-CoV-2 infection; however, there are no data available to support this hypothesis.

Considering the early stage of development of this study and the limited number of participants, a conservative approach has been adopted. Patients with symptomatic infections (including COVID-19) at screening will be excluded. Participants enrolled in this study will be closely monitored for new/emerging infections. Specific guidelines are provided in Section 8.2.8. In addition, vaccinations (including SARS-CoV-2/ COVID-19 vaccination if available) would need to be completed at least 4 weeks before first dose (Tartey and Thirumala-Devi 2019).

More detailed information about the known and expected benefits in the context of potential risks and reasonably expected adverse events (AEs) of RO7486967 is provided in the IB. Due to the short treatment duration and the nature of UC, there is no expected therapeutic benefit to the participants of Study BP43099.

**3. OBJECTIVES AND ENDPOINTS**

The objectives and corresponding endpoints are provided in Table 3.

**Table 3 Objectives and Endpoints**

|  | **Objectives** | **Endpoints** |
| --- | --- | --- |
| **Primary** | • To assess the safety and tolerability of orally administered RO7486967 in participants with active UC.  • To investigate the PK of orally administered RO7486967 in blood of participants with active UC. | • Incidence and severity of adverse events.  • Changes in vital signs, ECG parameters, and clinical laboratory safety parameters.  • Pharmacokinetic parameters of RO7486967 (and its metabolites, as applicable) in  blood by NCA and/or population  PK analysis. |
| **Secondary** | • To evaluate the effects on inflammation markers. | • Changes in CRP in blood and calprotectin in stool. |
| **Exploratory** | • To assess changes in PD markers in tissue and in stool in response to RO7486967.  • To assess changes in cellular compositions and gene expression in rectal tissue.  • To assess the inhibition of cytokine release after lipopolysaccharide (LPS) stimulation ex vivo in blood of patients treated with RO7486967.  • To explore the association of the microbiome composition with PD and safety of RO7486967.  • To assess the concentration of RO7486967 and its metabolites, as applicable, administered orally in rectal tissue of participants with active UC. | • **Rectal Tissue**: PK and PD biomarker such as mature IL-1β, cleaved caspase-1, cleaved gasdermin D, and cellular differences and function of individual cells.  • **Stool**: PD biomarkers such as mature IL-1β, microbiome composition.  • **Blood**: Cytokines (e.g., IL-1β and IL-18), ex vivo cytokine release (e.g., IL-1β). |

**4. STUDY DESIGN**

**4.1 OVERALL DESIGN**

Study BP43099 is a randomized, placebo-controlled, Investigator- and patient-blind, Sponsor-open study to assess safety, tolerability, and PK of RO7486967 in patients with active, moderate to severe UC. The study will utilize two treatment arms: placebo versus

450 mg RO7486967 administered orally QD.

A total of 18 participants are expected to be recruited, with approximately 12 receiving

450 mg RO7486967 and approximately 6 receiving placebo.

All participants in the study will have been diagnosed with UC previously and be in an active stage of their disease.

After the screening period, participants will be randomized to receive either placebo or RO7486967 orally (3 capsules of 150 mg). Randomization will be 2:1 (RO7486967 to placebo) and occur on Day −1. Treatment duration will be 7 days. Participants will have biopsies taken from the rectum (rectoscopy) between Day −3 and Day −1 and on Day 7 pre-dose (see Figure 1).

Participants will be hospitalized from Day −1 to Day 7. They will return to the clinic for the follow-up visit on Day 14 ± 3 days.

Dose adjustments are not foreseen during the study.

**4.1.1 Length of the Study**

The study length will be approximately 6 weeks (from screening through to follow-up), for each enrolled participant, as follows:

Screening: Up to 28 days. Treatment period: Days 1 to 7.

Follow-up: 7 (± 3) days after last study treatment administration.

**4.1.2 Stopping Rules Criteria**

The study will be put on hold pending a full safety review by the Sponsor, if any of the following occurs:

• A minimum of three Grade 3 serious AEs (SAEs) in three participants (at least one in each) considered to be related to RO7486967.

• At least one SAE ≥ Grade 4 (see NCI CTCAE v5.0), considered to be related to

RO7486967.

• Other clinically significant events (e.g., AEs or laboratory abnormalities) that in the opinion of the Investigator and the Sponsor preclude continued dosing.

• Decision by the Sponsor.

If moderate or severe AEs/SAEs are consistently observed across participants, or in case of unacceptable pharmacological effects that are reasonably attributable in the opinion of the Investigator to study treatment, then the dosing could be temporarily halted, with no further participants dosed until completion of a full safety review of the study. Relevant reporting and discussion with the Medical Monitor, relevant site personnel, and the Institutional Review Boards (IRB)/Independent Ethics Committees (IEC) would take place before dosing resumed. In the event of such an AE, every effort will be made to obtain a contemporaneous blood sample for PK analysis.

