**4.1.3 Individual Stopping Criteria**

Dosing will be discontinued in an individual participant in case of:

• AST or ALT elevation of ≥ Grade 2 considered to be related to RO7486967.

• Serious and/ or severe, medically significant RO7486967-related AEs.

• Infection with SARS-CoV-2.

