**Table 5 Guidelines for Managing Liver Function Test Abnormalities**

| **Abnormality* Action to Be Taken** |
| --- |
| Grade 1 AST or ALT • Continue study treatment  elevation or • Collect a sample for exploratory safety biomarkers  AST/ALT > ULN to  ≤ 3 × ULN • Monitor LFT (i.e., AST, ALT, ALP, TBL) every 3 days until  values resolve to normal or baseline value. |
| Grade 2 AST or ALT • Discontinue study treatment  elevation or • Monitor LFT (i.e., AST, ALT, ALP, TBL) every 48-72 hours  AST/ALT > 3 to ≤ 5 × ULN until values resolve to normal or baseline value.  • Collect a sample for exploratory safety biomarkers  • Events > 5 days duration:  o Obtain hepatology consultation; evaluate etiology. |
| Grade 3 AST or ALT • Discontinue study treatment  elevation or • Monitor LFT (i.e., AST, ALT, ALP, TBL) every 24-48 hours  AST/ALT > 5 to ≤ 20 × ULN until decreasing and then follow every 48-72 hours  • Collect a sample for exploratory safety biomarkers  • Events > 5 days duration:  o Obtain hepatology consultation; evaluate etiology. |
| Grade 4 AST or ALT • Discontinue study treatment elevation or  AST/ALT > 20 × ULN • Follow management guidelines as described for Grade 3  event. |
| AST or ALT ≥ 3 × ULN in • Consider event an AE of special interest (potential Hy’s law combination with total case) and report *immediately, without undue delay* (see bilirubin ≥ 2 × ULN or Appendix 3, Section 6).  clinical jaundice as defined  by Hy’s law • Collect a sample for exploratory safety biomarkers  • Permanently discontinue study treatment.  • Repeat LFT (i.e., AST, ALT, ALP, TBL) every 24-48 hours to confirm the abnormalities and to determine if they are increasing or decreasing and then follow every 48-72 hours.  • Monitor participant closely for clinical signs and symptoms  • Events > 5 days duration:  o Obtain hepatology consultation; evaluate etiology. |

AE = adverse event; ALP = alkaline phosphatase; ALT = alanine transaminase; AST = aspartate transaminase; LFT = liver function test; NCI CTCAE = National Cancer Institute Common Terminology Criteria for Adverse Events; TBL = total bilirubin; ULN = upper limit of normal.

*AE grading based on NCI CTCAE (v5.0).

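### Both counted study-hold triggers in Section 4.1.2 require a related SAE, so a related non-serious Grade 4 AST/ALT elevation, or one related potential Hy's-law case below Grade 4, pauses dosing of others only by judgement

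*Combined protocol and SAP*

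**What the plan says.** Section 4.1.2 of the protocol lists four reasons to put the study on hold pending a Sponsor safety review.

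- Bullet 1: "A minimum of three Grade 3 serious AEs (SAEs) in three participants (at least one in each) considered to be related to RO7486967".
- Bullet 2: "At least one SAE ≥ Grade 4 (see NCI CTCAE v5.0), considered to be related to" RO7486967.
- Bullet 3: "Other clinically significant events (e.g., AEs or laboratory abnormalities) that in the opinion of the Investigator and the Sponsor preclude continued dosing".
- Bullet 4: a decision by the Sponsor.

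The closing paragraph adds that if moderate or severe events are seen consistently across participants, or pharmacological effects are unacceptable, "then the dosing could be temporarily halted".

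The liver rules elsewhere act on the individual. Section 4.1.3 stops dosing in a participant with "AST or ALT elevation of ≥ Grade 2 considered to be related to RO7486967". Table 5 sets the transaminase bands: Grade 2 is "AST/ALT > 3 to ≤ 5 × ULN", Grade 3 is "AST/ALT > 5 to ≤ 20 × ULN", and Grade 4 is above 20 × ULN. Its Hy's-law row begins at "AST or ALT ≥ 3 × ULN in" combination with total bilirubin of at least 2 × ULN or clinical jaundice. It requires immediate reporting and permanent discontinuation for that participant.

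Appendix 2 Section 3.1 has severity and seriousness judged separately. Footnote d to Table 1 there makes Grade 4 and 5 events SAEs, but makes an exception for Grade 4 laboratory abnormalities unless a seriousness condition is met. Appendix 3 Section 6 treats the Hy's-law pattern as a marker of severe liver injury and allows it to be reported either as an SAE or as a non-serious event of special interest.

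**The concern.** A study-level hold protects people who have not yet been dosed. In 4.1.2 the part of that protection that works without judgement about the hold itself depends on an event being classed as an SAE. Two liver events can escape that classification or fall short of the count.

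The first is a related AST/ALT above 20 × ULN. A non-laboratory Grade 4 event judged related would trigger bullet 2. The laboratory equivalent need not.

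The second is one related potential Hy's-law case whose grade is below 4. The protocol itself regards this pattern as signalling severe liver injury, yet one case cannot meet either counted bullet.

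This is the first study of the drug in ulcerative colitis, and Section 2.3 lists hepatotoxicity as a potential risk. The design sections describe no sentinel or staggered dosing, so the next participant could be dosed before anyone has been required to pause.

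**Working it through.** **Step 1: trace each event through the two counted bullets.** All events are taken as judged related to RO7486967.

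| Event | Bullet 1 (three Grade 3 SAEs in three people) | Bullet 2 (one SAE of Grade 4 or higher) |
|---|---|---|
| AST/ALT > 20 × ULN, non-serious | Not met | Not met |
| AST/ALT > 20 × ULN, serious | Not met | Met |
| One Hy's-law case, reported as non-serious | Not met | Not met |
| One Hy's-law case, Grade 2 SAE | Not met | Not met |
| One Hy's-law case, Grade 3 SAE | One of three needed | Not met |
| One Hy's-law case, SAE of Grade 4 or higher | Not met | Met |

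The Hy's-law row in Table 5 starts at 3 × ULN, so by transaminase bands a case can sit in Grade 2 or Grade 3. If a diagnosis is recorded instead, its own grade applies.

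**Step 2: size.** The plan states no operating characteristics for the hold rule, so there is no figure to reproduce. From the documents: 18 participants at 2:1, so 18 × 2/3 = 12 on RO7486967 (Section 9.2). Assumed, because the documents give no values: p, the rate of each related event type per participant; s, the share of Grade 4 AST/ALT cases classed serious; independence between participants; and no overlap between Grade 4 and Hy's-law cases. Bullets 3 and 4 are not modelled.

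*Grade 4 AST/ALT.* At least one case: 1 − (1 − p)^12. Bullet 2 fires: 1 − (1 − ps)^12. The difference is the unmatched chance.

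| p | At least one case | Unmatched, s = 0.5 | Unmatched, s = 0.9 | Unmatched, s = 1 |
|---|---|---|---|---|
| 1% | 11.4% | 5.5 points | 1.1 points | 0 |
| 2% | 21.5% | 10.2 points | 1.9 points | 0 |

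*Hy's law below Grade 4.* At least one case at 1% and 2%: again 11.4% and 21.5%. Bullet 2 cannot fire. Even if every case were a Grade 3 SAE, bullet 1 would fire on these cases alone with binomial probability P(X ≥ 3), n = 12, which is 0.02% and 0.15%.

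**Step 3: effect of adding both events to bullet 2.** With the same p for each event type, the amended bullet fires with chance 1 − (1 − 2p)^12, against 1 − (1 − ps)^12 now.

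- p = 1%, s = 0.5: (1 − 0.98^12) − (1 − 0.995^12) = 21.5% − 5.8% = 15.7 points.
- p = 2%, s = 0.5: (1 − 0.96^12) − (1 − 0.99^12) = 38.7% − 11.4% = 27.4 points (from unrounded values).
- At s = 1 the same calculation gives 21.5% − 11.4% = 10.2 points (from unrounded values) and 38.7% − 21.5% = 17.2 points. All of this comes from Hy's-law cases.

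These are both the gap closed and the price paid. They are upper figures for truly new holds, since bullets 3 and 4 would already produce some of them.

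**The case against.** The strongest reply is that the plan already covers these events. Bullet 3 names laboratory abnormalities and, once the opinion is formed, the hold is mandatory. Bullet 4 lets the Sponsor act alone. Hy's-law cases go to the Sponsor immediately, the Sponsor undertakes to evaluate them promptly, and the Medical Monitor is reachable at all hours. Section 4.1.3 and Table 5 stop the affected participant from Grade 2. All of this stands. It means a hold is possible and likely to be considered; it does not make one automatic.

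Second, many of these events would be SAEs. Footnote c to the severity table requires an event judged medically significant to be reported as serious, Appendix 2 Section 2 leans the same way, and prolonged inpatient stay is a plausible route. Nothing in the documents supports s = 0.5, and at s = 1 the Grade 4 gap vanishes. This also stands, but it does not help a single Hy's-law case of Grade 2 or 3, which triggers nothing even as an SAE.

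Third, relatedness remains an Investigator judgement under any wording. True: the amendment removes one layer of discretion, not all of it.

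Fourth, the prior liver evidence is mostly reassuring. Section 2.3 reports mild transaminase increases in 4 of 18 treated healthy volunteers, without clear dose dependency and judged not clinically significant. It also describes low potential in vitro and no signs in the long-term animal studies. That limits urgency.

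A reader might infer that bullet 1 should be widened too, since non-serious Grade 3 elevations never count towards it. The documents do not support going that far. Bullet 1 asks for seriousness of every Grade 3 event alike, so laboratory values are not singled out as they are at Grade 4. The closing paragraph also addresses severe events seen across participants. Nor would the cost be trivial. If other related Grade 3 SAEs and Grade 3 liver elevations each had an assumed 5% rate, with half the liver events serious, widening would raise the chance that bullet 1 fires from 5.3% to 10.5%, or 5.1 points from unrounded values.

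**Conclusion.** The point holds as a modest, inexpensive safety improvement. For a related non-serious AST/ALT above 20 × ULN, and for one related potential Hy's-law case below Grade 4, no counted trigger in 4.1.2 applies, and a pause in dosing others rests on bullets 3 and 4 or the permissive closing paragraph.

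The reading of the rules rests on the text alone. The size does not: the event rates and the serious share are assumptions. The Hy's-law part is the firmer one, because it survives even if every case is classed as a Grade 3 SAE. The Grade 4 part shrinks to nothing as the serious share approaches 1.

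Two stronger readings should be resisted. A reader might infer that the protocol cannot hold the study for a liver laboratory signal; bullet 3 shows that it can. A reader might also infer that participants with liver injury are left on treatment; Section 4.1.3 and Table 5 rule that out for related cases. Nor should the change be described as adding only slightly to the chance of a hold: at the illustrative rates used to show the gap, the addition is roughly 16 to 27 points with s = 0.5.

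**What to change.** Amend only bullet 2 of Section 4.1.2. Keep its present condition and add two alternatives, so that any one of the following, if judged related to RO7486967, holds the study:

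- an SAE of Grade 4 or above (as now);
- one AST or ALT value above 20 × ULN, whether or not serious;
- one potential Hy's-law case, whatever its grade or seriousness, defined as AST or ALT ≥ 3 × ULN with total bilirubin ≥ 2 × ULN or clinical jaundice, where neither cholestasis nor another cause explains the raised bilirubin.

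Apply the bilirubin qualifier to this hold trigger only. It prevents a hold caused by Gilbert's disease, which exclusion criterion 27 allows. Do not add it to the Hy's-law row of Table 5, because that would narrow an existing reporting and discontinuation rule. Leave bullets 1, 3 and 4 as they are.

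The cost is a one-bullet wording amendment using laboratory values already collected, with the existing Sponsor review and no new committee or sample. The downside is the higher chance of a temporary hold computed above. It depends on the true rates, and each such hold would follow an event that merits a look before the next participant is dosed.
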